# Project Safe Guard–Trauma (PSG-T): Protocol for a randomized controlled trial of lethal means safety counseling to promote secure firearm storage among individuals with PTSD

**DOI:** 10.1016/j.conctc.2025.101549

**Published:** 2025-09-10

**Keywords:** Clinical trial, Suicide, Firearms

## Abstract

Firearm injury is the most common suicide method. When firearms are stored in a non-secure manner (e.g., unlocked, loaded), risk for suicide may be elevated. Accordingly, clinical, public health, and firearm industry stakeholders recommend efforts to promote secure firearm storage, such as lethal means safety counseling (LMSC). One LMSC intervention, Project Safe Guard (PSG), has demonstrated efficacy in prompting use of firearm locking devices in a sample of military service members; however, subsequent analyses show that PSG has diminished efficacy for individuals with elevated symptoms of posttraumatic stress disorder (PTSD). PTSD, characterized in part by hypervigilance to threat, is associated with elevated suicide risk as well as a greater likelihood of storing firearms using less secure methods. In response, our group developed an adaptation of PSG, termed Project Safe Guard-Trauma (PSG-T). This paper describes the design, methodology, and protocol of a randomized controlled trial comparing PSG-T to PSG among adults who screen positive for PTSD related to a victimization trauma (e.g., physical assault, sexual assault, combat) and who do not currently store all their personally owned firearms in a secure manner. PSG and PSG-T will be delivered by licensed clinical psychologists. Assessments will occur at pre-intervention, post-intervention, and 1-, 3-, and 6-month follow-up. The primary objective is to determine the efficacy of PSG-T in prompting greater beliefs and practices regarding secure storage of personal firearms.

## Introduction

1

Firearm injury is the most common suicide method in the United States [1]. Dozens of case-controlled and ecological studies have shown that access to firearms is associated with increased suicide risk [[2], [3], [4], [5]]. The suicide risk conferred by firearm access persists even after accounting for other suicide risk factors, such as mental illness [[6], [7], [8]]. Among firearm owners, the way in which firearms are stored—for instance, loaded with ammunition and/or unlocked—may also associated with suicide risk [2,5].

To reduce the risk of firearm suicide, multiple stakeholders—spanning clinical, firearm industry, governmental, and non-profit sectors—recommend that firearms be stored securely [[9], [10], [11], [12]]. Secure firearm storage involves a range of possible behaviors, including storing a firearm unloaded, locked, separate from ammunition, and in a secure location [13]. Secure firearm storage can also include voluntarily moving a firearm out of the home for safekeeping with a friend, family member, gun shop, police station, or other community partner [14,15]. A prominent approach to encouraging secure firearm storage is delivery of lethal means safety counseling (LMSC). LMSC refers to guided discussions, often by a clinician, to encourage an at-risk individual to reduce access to firearms and other lethal methods of suicide [13,16].

Project Safe Guard (PSG) is a LMSC intervention delivered through a brief interaction that uses motivational interviewing (MI) principles to encourage behavior change [17]. A randomized controlled trial (RCT) compared the efficacy of PSG, either alone or in combination with the provision of firearm cable locks, in prompting secure storage practices compared to a health counseling control among 232 firearm-owning military service members [17]. At 6-month follow-up, PSG outperformed the control intervention in prompting new use of locking devices (55.0 % vs. 39.0 %; OR = 1.91, 95 % CI = 1.10–3.32), and the combination of PSG and cable lock provision was not superior to either intervention alone. However, a secondary analysis of the PSG RCT found that the intervention-related benefits were attenuated for participants with elevated posttraumatic stress disorder (PTSD) symptoms [18]. This is especially concerning considering research demonstrating that individuals with PTSD are significantly more likely than individuals without PTSD to think about, attempt, and die by suicide [[19], [20], [21], [22]].

There are multiple reasons why the efficacy of safety interventions, such as PSG, may have differential impacts on patients with PTSD. PTSD affects safety perceptions and firearm storage practices (Fig. 1) [23]. PTSD is characterized by symptoms that have their onset or worsen following exposure to a traumatic event, persist for at least one month, and cause clinically significant distress or impairment [24]. The core symptoms of PTSD span four primary domains—intrusions, avoidance, negative alterations in cognitions and mood (e.g., beliefs that the world is unsafe), and marked alterations in arousal and reactivity/hyperarousal (e.g., being “on guard” for potential dangers). Individuals with PTSD, versus those without PTSD, report stronger beliefs that firearms protect from victimization [25], and individuals who report protection from others as a primary reason for firearm ownership, versus those who do not, are more likely than others to store their firearms non-securely [23,[26], [27], [28]]. In a sample of 327 firearm-owning military service members, elevated levels of PTSD hyperarousal symptoms were associated with increased odds of storing a firearm loaded and in a non-secure location [29].

**Fig. 1 fig1:**
[figure not shown]
Theoretical model of impact of PTSD symptoms on firearm storage practices.

Given that greater PTSD symptoms are associated with greater likelihood of non-secure firearm storage practices and existing LMSC interventions, namely PSG, demonstrate diminished efficacy in the setting of elevated PTSD symptoms, LMSC needs to be adapted for use in PTSD populations. The lack of evidence-based approaches for LMSC among individuals with PTSD likely contributes to gaps in care. In one study of 339 clinical psychologists, only 15% reported providing firearm-specific LMSC to their patients with PTSD [30]. In response, we developed an adaptation of PSG, termed Project Safe Guard-Trauma (PSG-T), designed for use with individuals who have PTSD to promote secure firearm storage practices, thereby reducing the risk of firearm-related harms such as suicide. PSG-T extends the MI practices demonstrated to be effective in PSG by exploring and addressing, including with psychoeducation, the potential functional link between trauma exposure and PTSD symptoms with firearm storage practices.

This paper describes the design, methodology, and protocol of an RCT examining the efficacy of PSG-T compared with PSG among firearm-owning individuals who screen positive for PTSD related to a victimization trauma (e.g., physical assault, sexual assault, combat, captivity). The overarching goal of the study is to expand the applicability of LMSC across at-risk populations, including individuals with PTSD for whom existing interventions demonstrate diminished efficacy. Secondary objectives are to evaluate a potential mechanism of change and heterogeneity of treatment effects (HTEs).

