#### Statistical analysis for primary outcome

3.9.1

The primary endpoint will be analyzed using a generalized linear mixed model (GLMM) with a logit link with a random intercept per participant (Hypothesis 1a). The actual firearm storage practice score at the 6-month follow-up assessment is a continuous value from 0 to 4. The primary outcome is the improvement from baseline, which is a binary transformation of the score. It measures whether the difference between the 6-month and baseline scores is >0. If the score difference exceeds 0, the transformed primary outcome is 1 (and 0 otherwise). We will model the primary outcome (improvement at 6 months) using a GLMM with a logit link, incorporating longitudinal information from all follow-up time points. This model accounts for the missingness of measurements at follow-up time points. Similar to the 6-month score, we will include dichotomized scores from post-intervention, 1-month, and 3-month measures in the GLMM with a random intercept representing each participant. The treatment effect of PSG-T will be compared between the two arms, with terms for intervention arm, baseline firearm storage practice scores, interaction between intervention and the follow-up time points, interaction between baseline score and follow-up time, and other covariates specified *a priori*. This model formulation was found to have the least amount of bias when baseline measures were subtracted from follow-up measures and patients had differential missingness of follow-up measures between intervention and control groups [45]. There are no interim analyses planned.

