#### Statistical analysis for secondary outcomes

3.9.2

Secondary endpoints include evaluating the efficacy of PSG-T compared with PSG on knowledge about the link between firearm storage practices and suicide risk and intentions to store firearms securely (Hypothesis 1b and 1c). We will use GLMM with an appropriate link function and a random intercept per participant to model the between- and within-group differences of outcomes over time [46]. For secondary outcomes reported in Likert scales, we will conduct sensitivity analysis by treating them as ordinal outcomes in the cumulative logit mixed model. To prevent model convergence issues in the cumulative logit model, we will assess the distribution of the ordinal by each category's relative proportions and pre-specify whether we will analyze the raw scale or merged category scores. We will use causal mediation analysis to evaluate PTSD-related negative cognitions about the world as a potential mechanism of change in PSG-T for increasing knowledge, intentions, and behaviors regarding safe firearm storage practices (Hypothesis 2) [47].

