#### Power

3.9.5

This study is powered according to the standardized effect size, Cohen's h, of the primary endpoint without considering correlations between longitudinal measures, which will provide a larger (more conservative) sample size estimate than if the study was powered based on the longitudinal correlation estimate in a GLMM [51]. Cohen's h is the standardized effect size for the between-group difference in proportions and is not affected by control group proportions [51,52]. Based on our preliminary result of the proportion of new uses of firearm locking devices in the intervention group (PSG-T, 30% = 55%–25%) and the control group (11.5% = 39%–27.5%), we calculated a Cohen's h of 0.47. A sample size of 150 (75 in each group) produces 80% power (α = 0.05) to detect a Cohen's h of 0.47 in measuring the between-group differences of proportions of reported new secure firearm storage behaviors. The proposed sample size of *N* = 168 participants (84 in each group) allows us to have >80% statistical power for the primary analysis and will yield 80% power to detect any subgroup-specific effect or standardized secondary outcomes of 0.47 or greater between PSG-T and control. The power will be at least 60% if the standardized subgroup-specific effect size is at least 0.35.

We used Monte Carlo simulation with 1000 replications to assess the power of *N* = 168 for the secondary outcomes, namely the mediation analysis of the PTSD-World in the PSG-T effect to increase knowledge, intentions, and behaviors regarding safe firearm storage practices [53]. Assuming the outcome standard deviation is 0.5, direct effect of PSG-T on PTSD is 0.6 and direct effect of PTSD on outcomes is 0.5, and the standard deviation is 1.3 for PTSD-World from Sexton et al. [54], a sample size of 168 allows us to detect a mediation effect of 0.30 (in Cohen's h scale) with 86 % power (α = 0.05).

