### Consideration of alternative study designs

4.1

There are five primary study design considerations that warrant mention (see Table 3).

**Table 3 tbl3:** Considerations of alternative study designs.

Consideration	Decision and Rationale
**Inclusion Criteria: Positive PTSD Screen vs. PTSD Diagnosis**	We elected to screen for PTSD using the PC-PTSD-5, consistent with PTSD screening recommendations in the VA/DOD CPG [55]. We considered whether to include participants with a PTSD diagnosis using the reference standard Clinician-Administered PTSD Scale for DSM-5 (CAPS-5) [56]. We decided to select individuals who screen positive for PTSD using the total PC-PTSD-5 for three reasons: (1) the PC-PTSD-5 is considerably briefer and more feasible to administer in the context of study inclusion screening (i.e., 5 vs. 60+ minutes); (2) assessing for symptoms rather than diagnoses aligns with findings from our pilot data indicating that existing LMSC have diminished efficacy for individuals with elevations on the total PCL-5 score [57]; and (3) this approach will align with clinical operations within the DOD, Veterans Health Administration, and other healthcare systems that typically rely on screening instruments such as the PC-PTSD-5 to make treatment-planning decisions.
**Inclusion Criteria: PTSD Symptoms Related to a Victimization Trauma**	We are limiting the sample to individuals who screen positive for PTSD related to their experience of a victimization trauma—that is, those that are interpersonal in nature, such as physical assault, sexual assault, or combat. Individuals who experience other traumatic events, such as natural disasters (e.g., hurricanes) or motor vehicle accidents, are ineligible unless they have also experienced a victimization trauma for which they screen positive for PTSD. We considered whether to limit participation on this criterion. However, unpublished evidence from our group suggests that among individuals with a victimization trauma history (but not an accident or injury trauma history), PTSD symptoms are associated with non-secure firearm storage practices.

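### The heterogeneity objective is supported only by power for an effect within a subgroup, which does not address whether the effect differs and which N = 168 does not deliver for any but a near-complete subgroup

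*Protocol article*

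**What the plan says.** The Introduction (section 1) sets two secondary objectives: "Secondary objectives are to evaluate a potential mechanism of change and heterogeneity of treatment effects (HTEs".

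Mechanism of change is then carried through the article. It has Aim 2 and Hypothesis 2 (section 2), causal mediation analysis (3.9.2) and a simulated power figure (3.9.5). Heterogeneity is not mentioned again in the aims or in sections 3.9.1 to 3.9.3. The primary model lists "interaction between intervention and the follow-up time points, interaction between baseline score and follow-up time, and other covariates specified" a priori. The secondary models are used "to model the between- and within-group differences of outcomes over time".

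The only later text that bears on heterogeneity is two power statements in 3.9.5. The planned 168 participants "will yield 80% power to detect any subgroup-specific effect or standardized secondary outcomes of 0.47 or greater between PSG-T and control", and "The power will be at least 60% if the standardized subgroup-specific effect size is at least 0.35". No subgroup, moderator or subgroup size is given.

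Section 4.1 (Table 3) cites pilot data that "existing LMSC have diminished efficacy for individuals with elevations on the total PCL-5 score". Table 2 shows that the PCL-5 is collected before the intervention.

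**The concern.** A test within a subgroup asks whether there is an effect in that subgroup. Heterogeneity asks whether the effect differs between subgroups, and that is a different parameter with a larger standard error. Power for the first says nothing about power for the second, so 3.9.5 gives the heterogeneity objective support that it does not have.

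The stated power also appears to use the full sample. A subgroup contains only part of the 84 per arm, so a claim of 80% for any subgroup cannot hold at the effect size for which the whole trial was sized.

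At stake is how the results will be read. A reader who trusts 3.9.5 would take a non-significant subgroup as informative, and would take a significant subgroup beside a non-significant one as evidence that PSG-T works for some people and not others. Section 3.9.3 makes no multiplicity adjustment for secondary analyses and relies on caution in interpretation.

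**Working it through.** **Inputs.** From 3.9.5: 30% versus 11.5%, h = 0.47, α = 0.05 (taken as two-sided, which reproduces the stated size), 75 per arm before and 84 per arm after allowance for loss, and the second effect size of 0.35. From 3.9.4: at most 10% missing at 6 months. Assumption: a binary moderator with equal split, since the article gives none; splits down to 25/75 are also shown.

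**The plan's own figures.** The article says of its rates: "the control group (11.5% = 39%–27.5%), we calculated a Cohen's h of 0.47". Check: h = 2·asin√0.30 − 2·asin√0.115 = 0.467.

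It then says: "A sample size of 150 (75 in each group) produces 80% power (α = 0.05) to detect a Cohen's h of 0.47". With p̄ = 0.2075, n = [1.96·√(2·0.2075·0.7925) + 0.84·√(0.30·0.70 + 0.115·0.885)]² / 0.185² ≈ 74.2, so 75 per arm (power 80.4%). Then 75/0.9 = 83.3, so 84 per arm and N = 168. Both sizes reproduce. On the arcsine scale 72 per arm suffice, and 75 give 82%.

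**Power within a subgroup.** Power = Φ(h·√(n/2) − 1.96), with n per arm in the subgroup.

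| Per arm | h = 0.47 | h = 0.35 |
|---|---|---|
| 84 (everyone) | 86% | 62% |
| 75.6 (everyone, 10% lost) | 82% | 58% |
| 42 (half) | 58% | 36% |
| 37.8 (half, 10% lost) | 53% | 33% |
| 21 (quarter) | 33% | 20% |

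Example: 0.47·√21 = 2.154; 2.154 − 1.96 = 0.194; Φ = 0.577.

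Reaching 80% at 0.47 needs 72 per arm in the subgroup (72/84 = 86% of the sample). Reaching 60% at 0.35 needs 80 per arm (80/84 = 95%). After 10% loss even the full sample falls short of 60% at 0.35.

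**Power for a difference between subgroups.** On the h scale, SE = √(2/n₁ + 2/n₂), where n₁ and n₂ are the numbers per arm in the two subgroups.

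- Equal halves of 84: SE = √(4/42) = 0.309. Detectable difference at 80% power = (1.96 + 0.84)·0.309 ≈ 0.86.
- After 10% loss: SE = √(4/37.8) = 0.325, and the detectable difference is about 0.91.
- Power for a difference of 0.47: Φ(0.47/0.309 − 1.96) ≈ 33%. For 0.35: about 20%.
- At a 25/75 split the detectable difference is about 1.00 (1.05 after 10% loss).
- For 80% power at a difference of 0.47: n per arm = 8·(1.96 + 0.84)²/0.47² ≈ 285, about 570 in total.

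**If heterogeneity were read from separate subgroup tests.** Suppose the true effect is 0.47 in both subgroups. The chance that exactly one is significant is p₁(1 − p₂) + p₂(1 − p₁).

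- Equal halves: 2·0.577·0.423 = 49% (50% after 10% loss). A simulation with binary outcomes gave 48.7%.
- 40/60: 50%. 30/70: 55%. 25/75: 58%.
- Common effect of 0.35: 44% to 50% over the same splits and loss.
- No effect in either subgroup: 2·0.05·0.95 = 9.5%.

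An interaction test has a nominal false-positive rate of 5%. The same simulation gave 5.9% with 42 per arm in each half.

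**The case against.** The strongest objection is that the article does not say how heterogeneity will be analysed. Section 3.9.5 is power text and does not refer back to the objective. Subgroup-specific effects are routinely estimated from a model with an interaction, so the phrase does not exclude one. Moderator lists and interaction terms for an exploratory objective commonly sit in the SAP or full protocol, which are not shown. All of this stands. A reader might infer that the trial will declare heterogeneity when one subgroup is significant and another is not, or that the lack of an interaction term in 3.9.1 to 3.9.3 is itself a defect. The document supports neither reading.

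It is also fair that the 49% depends on that unstated rule and on an assumed split, and that section 3.9.3 promises caution with secondary analyses.

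Making the PCL-5 the required moderator would also go too far. Table 3 cites it to justify screening rather than diagnosis. The earlier moderation finding concerned PSG against health counselling, not PSG-T against PSG. Everyone enrolled must score 4 or more on the PC-PTSD-5, which probably narrows the range of symptoms.

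None of this rescues the two power statements. They are positive claims in the article, they concern an effect inside a subgroup, and they fail on the article's own inputs whatever the SAP says.

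**Conclusion.** The point holds as a fault in 3.9.5. The only quantitative support for the heterogeneity objective addresses the wrong quantity. As stated it is also unattainable at h = 0.47 for any subgroup smaller than about 86% of the sample, and at 0.35 for any smaller than about 95%. With an equal split, power is about 58% and 36% in place of the stated 80% and at least 60%. For the question that heterogeneity poses, 80% power is available only for a difference of about 0.86 in h.

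The false-heterogeneity rate of 49% to 58% (splits from 50/50 to 25/75, common effect 0.47) is conditional. It shows why the method should be stated, not what the sponsor is known to intend. The power figures rest on the normal approximation on the h scale, a two-sided α of 0.05, a single binary moderator, and a comparison at one time point, which is how 3.9.5 itself sizes the trial.

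**What to change.** In 3.9.5, remove the two subgroup-specific power statements. The claim about standardized secondary outcomes can stay, since the full sample supports it (86% at 0.47, 82% after 10% loss). In their place, state that:

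- heterogeneity is assessed by the arm-by-moderator interaction on the 6-month contrast, reported with its confidence interval and labelled exploratory;
- effects within subgroups are descriptive, and no claim of differential benefit rests on them;
- for an equally split binary moderator, a difference of about 0.86 in h (0.91 after 10% loss) is detectable with 80% power, and power at 0.47 is about 33%.

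The sponsor should name the moderator or moderators. Pre-intervention PCL-5 total is a reasonable candidate, but the choice is the sponsor's. If it is kept continuous it needs its own detectable-effect figure, because 0.86 applies to a binary split.

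If the SAP already specifies interactions, only 3.9.5 needs aligning with it. The cost is wording: no further participants or measurements are needed if the moderator is one already collected. The price is an open statement that N = 168 can detect only large differences in effect.

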## Research aim and hypotheses

2

This study has two aims and related hypotheses. Aim 1 is to conduct a two-armed RCT to evaluate the efficacy of PSG-T compared with a control (the PSG intervention that does not focus on PTSD) in increasing knowledge about the link between firearm storage practices and suicide risk, intentions to store firearms securely, and secure firearm storage behaviors. Hypothesis 1 is that compared with control, at 1-, 3-, and 6-month follow-up, PSG-T will result in greater (a) adoption of secure firearm storage practices (primary outcome at 6-month follow-up), (b) knowledge about the link between firearm storage practices and suicide risk, and (c) intentions to store firearms securely.

Aim 2 is to evaluate differences in PTSD-related negative cognitions about the world as a potential mechanism of change in PSG-T for increasing knowledge, intentions, and behaviors regarding secure firearm storage practices. Hypothesis 2 is that participants who receive PSG-T will report fewer PTSD-related negative cognitions about the world compared with participants who receive PSG, and these decreases will be associated with increases in (a) adoption of secure firearm storage practices (b) knowledge about the link between firearm storage practices and suicide risk, and (c) intentions to store firearms securely.

